## 5.2 Product Formulation and Preparation

The individual components of DermaVir-LC002 will be supplied in vials as follows:

### **Cohort 1**

| Component | Content                | Concentration | Volume   | Appearance     |
|-----------|------------------------|---------------|----------|----------------|
| VIAL 1    | Plasmid DNA – pLWXu1   | 1 mg/mL       | 0.125 mL | Clear solution |
| VIAL 2    | PEIm                   | 13.6 mM       | 0.150 mL | Clear solution |
| AMPUL     | Dextrose solution, USP | 10%           | 5 mL     | Clear solution |

### **Cohort 2 and 3**

| Component | Content                | Concentration | Volume   | Appearance     |
|-----------|------------------------|---------------|----------|----------------|
| VIAL 1*   | Plasmid DNA – pLWXu1   | 1 mg/mL       | 0.425 mL | Clear solution |
| VIAL 2*   | PEIm                   | 13.6 mM       | 0.450 mL | Clear solution |
| AMPUL     | Dextrose solution, USP | 10%           | 5 mL     | Clear solution |

\* **Cohort 3:** Two vials each of DNA and PEIm will be provided for formulation of the high dose.

### 5.2.1 Source and Storage Conditions of Components

| Component              | Manufacturer                                                                                      | Storage                                  |
|------------------------|---------------------------------------------------------------------------------------------------|------------------------------------------|
| Plasmid DNA – pLWXu1   | Althea Technologies, Inc, San Diego, CA 92121, USA                                                | -80°C, when possible;
-20°C otherwise |
| PEIm                   | PolyPlus-transfection™, University of Strasbourg, School of Pharmacy Illkirch, Strasbourg, France | -80°C, when possible;
-20°C otherwise |
| Dextrose solution, USP | Abbott Laboratories, North Chicago, IL 60064, USA                                                 | 15 - 30°C                                |
| LC002                  | Trained personnel at clinical site                                                                | 4 °C                                     |

### 5.2.2 Other materials required for formulation

- 1-ml graduated syringes (2)
- Needles (21-gauge, 1 1/2" length) for formulation (2)

### 5.2.3 Procedures

This procedure is to be performed only by specifically trained individuals and should take place under aseptic conditions, such as in a pharmaceutical hood or laminar flow hood.

The following final manufacturing steps of LC002 should be completed within 3 hours of LC002 application. The DermaVir-LC002 Formulation Record (Appendix V), is to be filled out in the CRF when following this procedure.

1. Thaw frozen components for 30 minutes at room temperature.
2. Use a syringe and needle to transfer the dextrose solution to **Vial 1** (DNA):
  - Cohort 1: transfer 0.375 mL
  - Cohort 2: transfer 1.275 mL
  - Cohort 3: transfer 1.275 mL.
3. Use the same syringe and needle to transfer the dextrose solution to **Vial 2** (PEIm).
  - Cohort 1: transfer 0.450 mL
  - Cohort 2: transfer 1.350 mL
  - Cohort 3: transfer 1.350 mL

Discard syringe and needle after this step.
4. Both vials are inverted 10 times and then shaken down with a quick flick of the wrist so that as much of the solution as possible can be collected to the bottom of the vial and is not lost in the top.

5. Use a new syringe and needle to remove solution from **Vial 2** (PEIm):
- Cohort 1: remove 0.50 mL
  - Cohort 2: remove 1.70 mL
  - Cohort 3: remove 1.70 mL

and add this volume to **Vial 1** (DNA). Discard syringe and needle.

**Note:** It is important to add Vial 2 to Vial 1, and NOT Vial 1 to Vial 2, for optimal formation of the PEIm/DNA complexes.

6. **Vial 1** containing all components is inverted 10 times and shaken down with a quick flick of the wrist. The DermaVir product is then ready for administration.
7. Fill out the DermaVir-LC002 Formulation Record with the amounts and batch numbers of each component used and the time of formulation.
8. Label final product vial with the appropriate label stating the Formulated Batch # and time of expiration (3 hours after formulation).
9. Batch #'s are determined as follows:

| Date of formulation | Dash | Sequence of formulation for that day |
|---------------------|------|--------------------------------------|
| MMDDYY              | -    | XX                                   |

Example:

Batch # for the second formulation performed on January 5, 2004: 010504-02.

10. Immediately deliver vial along with Form #: OPF-2008 to the clinical site.
11. The final DermaVir product should be kept at 4°C and administered to the subject within 3 hours of formulation.

**Note:** The volume of DermaVir formulated here is sufficient for a single dose (Cohorts 1 and 2, low and medium dose, respectively). Cohort 3 (high dose) requires two separate formulations to produce the volume of DermaVir required for a single dose.

Quantitative composition of the final dosage:

| Dose          | PEIm
(13.6 mM,
aqueous solution)* |                  | DNA
(1mg/mL, aqueous
solution) |                  | Dextrose
(100 mg/mL,
aqueous solution) |                  | Dose of
LC002 | Treated skin
area   |
|---------------|-----------------------------------------|------------------|--------------------------------------|------------------|----------------------------------------------|------------------|------------------|------------------------|
|               | Volume
(ml)                          | Quantity
(mg) | Volume
(ml)                       | Quantity
(mg) | Volume
(ml)                               | Quantity
(mg) |                  |                        |
| Low    | 0.1                                     | 0.000069         | 0.1                                  | 0.1              | 0.6                                          | 60               | 2 x 0.4 ml       | 2 x 80 cm  |
| Medium | 0.4                                     | 0.000276         | 0.4                                  | 0.4              | 2.4                                          | 240              | 4 x 0.8 ml       | 4 x 80 cm  |
| High   | 0.8                                     | 0.000552         | 0.8                                  | 0.8              | 4.8                                          | 480              | 8 x 0.8 ml       | 8 x 80 cm  |

\*This concentration is calculated based on the monomer of ethylenimine and 5% mannosilation (MW= 42 (MW of EI) x 180 (MW of mannose) x 0.05 (5% mannose) = 51. Therefore, 0.1 ml 13.6 mM PEIm has 69 ng PEIm.

### 5.3 Product Supply, Distribution, and Pharmacy

#### 5.3.1 Study Product Acquisition

LC002-DermaVir will be provided by the Sponsor.

Antiretrovirals will not be supplied by the study and will need to be obtained by the subject.

### 5.4 Concomitant Medications

#### 5.4.1 Required Medications

Subjects will be required to be on a stable regimen of HAART (containing drugs of at least two different classes), and remain on it while on study, that suppresses plasma HIV-1 RNA to < 50 copies/mL.

#### 5.4.2 Prohibited Medications

The concomitant use of the following immunomodulatory therapies, which have potential putative effects on immunologic and/or virologic indices, are prohibited while on study:

- Systemic (IV and po) corticosteroids
- Thalidomide
- Cyclosporin
- Interferons
- Interleukins
- IgG-containing products

- Cimetidine (Tagamet)
- Acetylcysteine (NAC)
- Sargramostim (GM-CSF)
- Dinitrochlorobenzene (DNCB)
- Thymosin alpha 1 (thymosin alpha)
- Thymopentin
- Inosiplex (Isoprinosine)
- Polyribonucleoside (Ampligen)
- Ditiocarb sodium (Imuthiol)
- Experimental HIV vaccines

#### 5.4.3 Precautionary Medications

- Treatment with topical corticosteroids is allowed except in close proximity to the vaccination sites in the 2 weeks prior to each vaccination.
- Use of local skin treatments is allowed, except in the targeted vaccination sites within 7 days of the vaccination. During this period, subjects should avoid manipulation of vaccinated areas to enable monitoring of possible vaccine related toxicity. Sites may be rinsed with water, but soap and other possible irritants should be avoided. In the case of discomfort at the vaccination site, cold packs may be administered as needed. All other local treatments should only be administered after consultation with the investigator.

#### 5.4.4. Prohibited Activities

- Exposure to the sun (sunbathing, tanning bed) in the 2 weeks prior to vaccination.
- Laser hair removal at vaccination sites.

## 6.0 CLINICAL AND LABORATORY EVALUATIONS

The following clinical and laboratory evaluations will be performed at scheduled intervals as indicated below. A schema is provided in Section 6.1. Definitions and special instructions related to these evaluations are provided in Sections 6.2 and 6.3.

### 1. Screening evaluations – to be performed within three months of entry:

Signed informed consent, documentation of HIV-1 infection, medical history, medication history, nadir CD4 count, complete physical examination (including signs and symptoms, diagnoses, Karnofsky score, height, weight, skin and lymph node status, and vital signs). Laboratory: hematology, blood chemistries, liver function tests, autoantibodies (anti-ds-DNA, anti-nuclear antibody), urinalysis, urine pregnancy test, hepatitis B and C screen (hepatitis B surface antigen and anti-hepatitis C antibodies), HIV-1 RNA, CD4/CD8 count and CD45RA/RO.

### 2. Pre-entry evaluations – to be performed within 14 days of entry:

Laboratory: hematology, blood chemistries, liver function tests, urinalysis, HIV-1 RNA,

### 3. Treatment-phase – evaluations from Day 0 to Day 28:

- a. Medication history at Days 0, 28.
- b. Targeted physical examination at Days 0, 7, 14, 28.
- c. Complete physical examination at Day 28.
- d. Vaccine local site evaluations at Days 0 (immediately after removal of skin patch), 7, 14, 28.
- e. Hematology evaluations at Days 0, 7, 14, 28.
- f. Blood chemistries and liver function tests at Days 0, 7, 14, 28.
- g. Autoantibodies (ANA, anti-ds-DNA) at Day 28.
- h. Urinalysis at Days 0, 7, 14, 28.
- i. Urine pregnancy test at Day 0.
- j. HIV-1 RNA at Days 0, 7, 28.
- k. CD4/CD8 count and CD45RA/RO at Days 0, 7, 14, 28.
- l. Virus-specific immune responses: samples at Days 0, 14, 28.
- m. Plasma and PBMCs for storage at Days 0, 7, 14, 28.

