To further evaluate the vaccine in the setting of a controlled, randomized trial, 26 rhesus macaques chronically infected with SIV251 were randomized to receive 1) no therapy (control), 2) DermaVirSHIV, 3) STI-HAART (3 weeks on/3 weeks off therapy), or 4) DermaVirSHIV + STI-HAART. Unlike the seven animals receiving STI-HAART alone, the seven primates randomized to receive vaccine + STI-HAART progressively controlled viral rebound during treatment interruptions from a median 33,860 copies/mL to <200 copies/mL. The six macaques treated with vaccine alone did not experience an increase in viral load, in contrast to the untreated control animals. All treated cohorts, including the vaccine alone group survived longer than the untreated controls (71).

The studies in SIV-infected monkeys described here reflect the intended dose and schedule proposed in this protocol. In infected monkeys, 15 of 16 animals received at least 7 repeated vaccinations (one more than intended for the highest dose cohort of this protocol) of 0.1 mg DNA on a skin area of 40 sq cm, with two vaccinations spaced one week apart every six weeks. One animal received only four vaccinations, and was lost due to an SIV-related B cell lymphoma, not attributable to vaccination. All vaccinated animals showed improved survival compared to the untreated controls. In addition, it should be noted that these monkeys, weighing between 4 and 10 kg, were vaccinated on a large surface area (40 sq cm) relative to their body size, but showed only mild and transient local reactions at the treated skin sites. We conclude that repeat dosing with DermaVir was not associated with significant toxicity in these monkeys.

To confirm these findings, a GLP study was performed in swine to determine the local and systemic toxicity of DermaVir. Eighteen animals were randomized into 3 groups to receive 1) dextrose solution only, 2) dextrose+PEIm only, or 3) dextrose+PEIm+DNA (DermaVir). The dose and schedule reflect one vaccination series of the highest dose cohort in this protocol: 0.4 mg DNA applied at 4 sites of 160 sq cm each, with two doses spaced one week apart. All animals were followed to four weeks after the second vaccination. There were no observations of local or systemic toxicity associated with DermaVir treatment in this study. The only side effects observed were related to the shaving and skin preparation procedure, and were mild and transient in all cases.

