### 6.2.2 On-Study Evaluations

#### Entry

Evaluations should occur after enrollment prior to vaccine administration and at least 24 hours after the pre-entry evaluations.

All subjects will visit the clinic on the weeks  $\pm$  3 days indicated in the Schedule of Events. Vaccine administration has to occur on the weeks indicated in the Schedule of Events  $\pm$  0 days.

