#### 6.3.7 LC002 administration/evaluation

The first vaccine site evaluation (see section 7.1.1) will be performed immediately after removal of the skin patch (3h post application). Further vaccine site evaluation must occur on the days indicated in the Schedule of Events.

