#### 7.1.2 Systemic reactions

Systemic reactions will be graded according to the Division of AIDS Table for Grading Adult Adverse Experiences (see Appendix IV). The Principal Investigator should be contacted within 48 hours for any non-local Grade 3 or 4 reactions (for example, elevated temperatures following immunization) thought definitely, possibly, or probably related to vaccination with LC002.

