### 9.2 Endpoints

#### 9.2.1 Primary endpoint: Safety

Occurrence of at least one grade 3 or higher adverse event including signs/symptoms, lab toxicities and clinical events that is "possibly, probably," or "definitely" related to study treatment (as judged by the Principal Investigator, including site clinicians on the team) any time from the first day of study treatment until 28 days after LC002 administration.

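### No safety observation is scheduled between patch removal on Day 0 and the Day 7 visit, so short systemic reactions, chiefly fever, reach the primary endpoint only by recall or spontaneous report

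*Protocol*

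**What the plan says.** All references are to the protocol.

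- **Site evaluations.** Section 6.0, item 3d: "Vaccine local site evaluations at Days 0 (immediately after removal of skin patch), 7, 14, 28". Section 6.3.7 places the first of these 3 hours after application.
- **Examinations.** Section 6.0, item 3b: "Targeted physical examination at Days 0, 7, 14, 28". Section 6.3.6 includes oral temperature in this examination and ties it to anything new since the previous visit. Safety laboratory tests follow the same days.
- **Visit window.** Section 6.2.2: "All subjects will visit the clinic on the weeks" shown in the schedule, plus or minus 3 days.
- **Medication history.** During the treatment phase it is scheduled at Days 0 and 28 only (Sections 6.0 and 6.1).
- **Recording.** Section 6.3.6 (Signs and Symptoms) requires local reactions of every grade, and other signs or symptoms from Grade 2, to be entered in the CRF.
- **Systemic reactions.** Section 7.1.2 gives "elevated temperatures following immunization" as its example of a non-local Grade 3 or 4 reaction.
- **Endpoint and escalation.** Section 9.2.1 counts Grade 3 or higher events at least possibly related to treatment, "any time from the first day of study treatment until 28 days after LC002 administration". Section 9.1.3 allows escalation if no subject in the current or a lower cohort had such an event. Sections 4.3.1 and 9.1.3 let this happen once subjects have been followed for 14 days.

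**The concern.** The days right after dosing are when a short reaction to a vaccine could come and go, and in those days the schedule provides no prospective observation. A fever that rises and settles before the Day 7 visit is known only if the subject contacts the site or remembers it when asked. Without a measured temperature it cannot be placed on the Appendix IV scale, where Grade 3 is 39.6 to 40.5 °C.

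One indirect check is also late. Use of an antipyretic could reveal an early fever, but the first medication history after vaccination is due on Day 28, and the next cohort may open from Day 14.

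The primary endpoint is whether at least one qualifying event occurs, and a single event in a three-subject cohort blocks escalation. A missed or under-graded Grade 3 event therefore acts in one direction: toward no event recorded, toward escalation, and toward concluding that the dose is safe.

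**Working it through.** **1. Length of the gap.** Inputs: first look at 3 hours (Section 6.3.7), next look at Day 7 (Sections 6.0 and 6.1), window of 3 days either way (Section 6.2.2), read as applying to the Day 7 visit.

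- Nominal: 7 × 24 − 3 = 165 hours, about 7 days.
- With the window: 7 − 3 = Day 4 at the earliest, 7 + 3 = Day 10 at the latest.
- Share of the 28-day endpoint window: 7/28 = 25%. Share of the 14-day minimum before escalation: 7/14 = 50%.

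**2. What a Day 7 look can still see.** A reaction is visible at the look if onset ≤ 7 ≤ onset + duration, in days.

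- Onset at 12 to 72 hours with a duration of 3 days or less ends by 3 + 3 = Day 6 at the latest, so it is over before Day 7.
- Onset at 24 hours needs a duration of at least 7 − 1 = 6 days to be seen on Day 7.
- A visit on Day 4 does better: onset at 24 hours with a duration of 3 days is still visible.

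**3. Which events are exposed.**

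| Event | Basis for grading | Still gradable at Day 7? | Affects escalation? |
|---|---|---|---|
| Short fever, Grade 3 or higher | Measured temperature (Appendix IV) | No, unless someone measured it | Yes, if related |
| Local Grade 3 or 4 (ulceration, blistering, superinfection, phlebitis, necrosis) | The lesion (Section 7.1.1, Table 1) | Often, because the lesion may persist | Yes, if related |
| Local Grade 1 or 2 | Same skin findings, separated by symptoms (Table 1) | By recall of symptoms | No |

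**4. Possible effect on the escalation rule.** The protocol gives neither the true rate *p* of related Grade 3 or higher events per subject nor the probability *s* that such an event is captured. Both are assumed here. With 3 subjects per cohort (Schema, Sections 3.0 and 5.1.1):

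P(no event recorded in 3) = (1 − *p* × *s*)³

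Example: *p* = 0.20, *s* = 0.5 gives (1 − 0.10)³ = 0.729, against (1 − 0.20)³ = 0.512 with full capture.

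| Assumed *p* | *s* = 1 | *s* = 0.75 | *s* = 0.5 | Rise over full capture |
|---|---|---|---|---|
| 0.10 | 0.729 | 0.791 | 0.857 | 0.06 to 0.13 |
| 0.20 | 0.512 | 0.614 | 0.729 | 0.10 to 0.22 |
| 0.30 | 0.343 | 0.465 | 0.614 | 0.12 to 0.27 |

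Here *s* is capture over all qualifying events. If a share *f* of events falls wholly in the gap and a share *m* of those is lost, *s* = 1 − *f* × *m*. So *s* = 0.5 requires, for example, that every event falls in the gap and half are lost. *s* = 0.75 requires half and half.

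**The case against.** The strongest reply is that the protocol does not leave early events uncovered. Section 6.3.6 asks at each visit about new symptoms since the previous one and requires all toxicities to be documented. Section 5.4.3 requires the subject to consult the investigator before any local treatment other than cold packs. Section 6.3.3 has antipyretics and analgesics recorded with start and stop dates. A Grade 3 event is by definition severe and more likely to be reported than a mild one. Subject instructions could also sit in the consent form or CRF instructions, which are not shown. All of this stands as partial capture. None of it provides a temperature measured during the gap.

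Four stronger readings are tempting but not supported:

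- **That early reactions will simply be missed.** Recall and spontaneous report will recover some of them.
- **That the protocol itself expects short-lived endpoint events.** Section 2.2 says the monkeys "showed only mild and transient local reactions at the treated skin sites", and the swine effects were attributed to shaving and skin preparation. Those were mild reactions in animals; nothing there says that a Grade 3 reaction would be brief.
- **That local reactions cannot be graded once the skin has healed.** In Table 1, Grades 1 and 2 share the same skin findings and differ by symptoms, which can be asked about. Only Grade 3 and above rests on the lesion.
- **That Section 5.4.3 contradicts the schedule.** It says "subjects should avoid manipulation of vaccinated areas to enable monitoring of possible vaccine related toxicity" around the 7 days after vaccination, and site evaluations stand at both ends of that period. The stated aim is thinly served, but there is no contradiction.

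It is also fair that the 25% share alone proves little, since Days 14 to 28 are a longer interval between visits. What matters is that this gap directly follows dosing.

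**Conclusion.** The point holds in a limited form. From about 3 hours after application until a visit between Day 4 and Day 10, safety information depends on recall and spontaneous report, while the endpoint that controls escalation counts from the first day. The weak spot is short systemic reactions, chiefly fever. Grade 1 and 2 local reactions, which the protocol wants recorded, may also be lost, but they cannot change the escalation decision. Grade 3 and 4 local lesions may well still be visible at Day 7.

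The direction of any error is clear: toward no event. Its size is not known. The rise of about 0.06 to 0.27 in the chance of a clean three-subject cohort is an illustration resting on assumed true rates of 0.10 to 0.30 and assumed overall capture of 50 to 75%; it is not an estimate for this vaccine. This is a weakness in safety ascertainment that is cheap to repair, and the change should be made.

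**What to change.** Add to the Section 6.1 schedule a subject diary for Day 0 to Day 7, with a thermometer, covering daily temperature, symptoms at each vaccinated site, and systemic symptoms. Have it reviewed and graded at the existing Day 7 visit. State in Section 9.2.1 that diary events graded 3 or higher and judged related count toward the primary safety endpoint, so that they also enter the rule in Section 9.1.3.

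The cost is one diary page and a thermometer for each of 9 subjects, plus a CRF page. No visit or invasive procedure is added. The downside is that more Grade 1 and 2 events will be recorded, which should be expected when the cohorts are described.

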### 1.2 Secondary Objectives

- 1.2.1. To explore the immunogenicity of a LC002 for the treatment of individuals with chronic HIV-1 infection and HAART-induced durable suppression of viral replication.

- 1.2.1.1. To evaluate CD4+ and CD8+ T cell counts

- 1.2.1.2. To describe the distribution of HIV-specific immune responses with the following assays:

- Total HIV-specific lymphocyte count (CD3+ T-cells) using flow cytometric assay to detect antigen-specific IFN-gamma-producing cells that respond to whole Zn-finger-inactivated virus stimulation.
- HIV-specific CD8+ T cell count (CD8+, CD3+) using flow cytometric assay to detect antigen-specific IFN-gamma-producing cells that respond to whole Zn-finger-inactivated virus stimulation (1).

- 1.2.1.3. To explore whether LC002 treatment augments the magnitude of HIV-1 specific T-cell responses.

- 1.2.1.4 To explore whether increasing the dose of LC002 has greater efficacy in augmenting HIV specific T-cell responses in HIV-1 infected subjects.

- 1.2.1.5 To explore whether there are differences in longitudinal profiles of HIV-specific T-cell levels (and changes in T-cell levels from baseline) between treatment arms.

- 1.2.2. To monitor anti-DNA antibody response after immunization

- 1.2.3. To explore whether there are differences in the tolerability of LC002 with respect to pre-mature treatment discontinuation between treatment arms.
- 1.2.4. To explore if immunization results in any changes in viral load.

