## 4.0 SELECTION AND ENROLLMENT OF SUBJECTS

### 4.1 Inclusion Criteria

- 4.1.1 Ability and willingness of subject or legal guardian/representative to give written informed consent.
- 4.1.2 HIV-1 infection, as documented by any licensed ELISA test kit and confirmed by Western blot, HIV-1 culture, HIV-1 antigen, plasma HIV-1 RNA, or a second antibody test by a method other than ELISA is acceptable as an alternative confirmatory test at any time prior to study entry.
- 4.1.3 On a stable antiretroviral regimen (containing drugs of at least two different classes) without changes or interruptions for at least 24 weeks prior to study entry.
- 4.1.4 Plasma HIV-1 RNA level of less than 50 copies/mL, while on a stable antiretroviral regimen, obtained at least twice within the 12 weeks prior to study entry.
- 4.1.5 Peak plasma HIV-1 RNA level before initiation of HAART > 1000 copies/mL.
- 4.1.6 CD4 cell count > 300 cells/mm^3 within the 12 weeks prior to study entry.
- 4.1.7 Nadir (lowest) CD4+ cell count > 250 cells/mm^3 at any time prior to study entry.
- 4.1.8 The following laboratory values, obtained within 30 days prior to study entry:
  - Absolute neutrophil count (ANC)  $\geq 1000/\text{mm}^3$
  - Hemoglobin  $\geq 9.0$  g/dL
  - Platelet count  $\geq 50,000/\text{mm}^3$
  - Serum creatinine  $\leq$  upper limit of the laboratory normal range (ULN)
  - AST (SGOT), ALT (SGPT), and alkaline phosphatase  $\leq 2.5 \times \text{ULN}$
  - Total bilirubin  $\leq 2.5 \times \text{ULN}$

- Anti-nuclear antibody (ANA) titer of 1:40 or lower and negative for serum anti-double-stranded DNA antibody (anti-ds-DNA) test result at screening.

- 4.1.9 All women of reproductive potential (who have not reached menopause or undergone hysterectomy, oophorectomy, or tubal ligation) must have a negative urine  $\beta$ -HCG pregnancy test performed within 14 days prior to study entry.

Female study volunteers who are not of reproductive potential (who have reached menopause or undergone hysterectomy, oophorectomy, or tubal ligation) or whose male partner has undergone successful vasectomy with documented azoospermia or has documented azoospermia for any other reason, are eligible without requiring the use of contraception. Acceptable documentation of menopause, sterilization, and azoospermia is written or oral documentation communicated by clinician or clinician's staff of one of the following:

- Physician report/letter

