#### Screening

Screening evaluations to determine eligibility must be completed within **3 months** prior to study entry.

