#### 9.2.2 Secondary endpoints

The following endpoints will be observed at all on-study scheduled evaluation days (section 6.1).

- 9.2.2.1 Change in CD4+ T-Cell count/mL in PBMC from baseline values.
- 9.2.2.2 Change in CD8+ T-Cell count/mL in PBMC from baseline values.
- 9.2.2.3 Total HIV-specific lymphocyte count and percent (CD3+ T-cells) based on a flow cytometric assay to detect antigen-specific IFN-gamma-producing cells that respond to whole Zn-finger-inactivated virus stimulation: To measure changes in the magnitude of HIV-specific CD3+ immune responses in the blood induced by vaccination.
- 9.2.2.4. HIV-specific CD8+ T-cell count and percent (CD3+/CD8+) based on a flow cytometric assay to detect antigen-specific IFN-gamma-producing cells that respond to whole Zn-finger-inactivated virus stimulation:  
To measure changes in the magnitude of HIV-specific CD8+ immune responses in the blood induced by vaccination.
- 9.2.2.5. Tolerability: occurrence of premature study treatment discontinuation (i.e. less than three hours of patch application at all designated sites) due to subject/parent/guardian/physician requesting discontinuation even though no protocol-defined toxicity endpoint had been reached (e.g. grade 1 or 2 toxicity or refuses rechallenge for higher grade, if appropriate.)
- 9.2.2.5. To evaluate if anti-DNA antibody responses develop after immunization.
- 9.2.2.6 Whether HIV-1 RNA copies/mL is below 50 or not.

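### Anti-DNA antibody endpoint: no autoantibody test is scheduled between screening (up to three months before entry) and Day 28, and the schedule conflicts with the 30-day entry limit in 4.1.8

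*Protocol*

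**What the plan says.** The protocol names this outcome twice. Section 1.2.2 sets the objective "To monitor anti-DNA antibody response after immunization", and the second item numbered 9.2.2.5 sets the endpoint "To evaluate if anti-DNA antibody responses develop after immunization".

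Section 6.0 and the table in 6.1 agree on when autoantibodies are measured:

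- Screening, which is "to be performed within three months of entry", includes "autoantibodies (anti-ds-DNA, anti-nuclear antibody" (ANA).
- Pre-entry, within 14 days of entry, repeats the hematology, chemistry, liver and urine tests but not autoantibodies.
- Day 0 has no autoantibody test.
- The treatment phase has "Autoantibodies (ANA, anti-ds-DNA) at Day 28" only.
- Follow-up has one test, at Week 48.

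Section 6.2.1 repeats the outer limit: "Screening evaluations to determine eligibility must be completed within" three months.

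Inclusion criterion 4.1.8 is headed "The following laboratory values, obtained within 30 days prior to study entry". Its last bullet reads "Anti-nuclear antibody (ANA) titer of 1:40 or lower and negative for serum anti-double-stranded DNA antibody (anti-ds-DNA) test result at screening". Section 4.3.1 requires the entry criteria to be met at screening and again at pre-entry. Criterion 4.1.11 sets a 30-day limit for the Karnofsky score. Under 6.3.5 that score belongs to the complete physical examination, which 6.1 schedules before vaccination only at screening.

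**The concern.** The endpoint is a before-after comparison within each subject, so its value depends on how close the before result lies to vaccination. For plasma HIV-1 RNA (6.3.16) and CD4/CD8 counts (6.3.17) the protocol builds the baseline from the pre-entry and entry measurements. For autoantibodies, 6.3.12 names the two tests and gives no baseline, and no test is scheduled near entry.

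An antibody that arose between screening and Day 0 would first be seen on Day 28 and would look the same as one that arose after vaccination. There is no control arm and each cohort has three subjects, so the study offers no comparison to separate the two.

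There is also an eligibility problem. The schedule allows an autoantibody or Karnofsky result that is older than the inclusion criteria accept.

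**Working it through.** The plan states no figure for this interval, so there is none to reproduce. The check is calendar arithmetic and a comparison of sections.

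**Inputs.** Screening window: three months, taken as 90 to 92 days (6.0 item 1, 6.2.1). Limit in 4.1.8: 30 days. Pre-entry window: 14 days (6.0 item 2). First test after vaccination: Day 28 (6.0 item 3g). Sample size: 9, three per cohort.

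**Longest interval from last pre-vaccination test to Day 28.** Gap = days from that test to Day 0, plus 28. Pre-vaccination share = days before Day 0 divided by the gap.

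| Last test before vaccination | Gap (days) | Share before vaccination |
|---|---|---|
| Screening, three-month window only | 90 + 28 = 118 to 92 + 28 = 120 | 90/118 = 76% to 92/120 = 77% |
| Screening, 30-day limit enforced | 30 + 28 = 58 | 30/58 = 52% |
| Pre-entry test added | 14 + 28 = 42 | 14/42 = 33% |
| Day 0 test added | 0 + 28 = 28 | 0% |

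The visit window of plus 3 days in 6.2.2 would extend the first row to 121 to 123 days.

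**Size of the eligibility mismatch.** A screening result at the three-month limit is 90 − 30 = 60 to 92 − 30 = 62 days older than 4.1.8 accepts.

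**What the interval could mean (illustration only).** The protocol gives no background rate of conversion. Assume an annual rate r of 1%, 5% or 10%, independent between subjects. The chance of at least one conversion unrelated to vaccination among 9 subjects over d days is 1 − (1 − r)^(9d/365.25).

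| Assumed r | d = 28 | d = 58 | d = 120 |
|---|---|---|---|
| 1% | 0.7% | 1.4% | 2.9% |
| 5% | 3.5% | 7.1% | 14.1% |
| 10% | 7.0% | 14.0% | 26.8% |

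**Sections side by side.**

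- 4.1.8 contains both a 30-day heading and a bullet tied to screening. The two agree only if screening falls within 30 days of entry, and nothing requires that.
- 4.3.1 asks for eligibility at two visits. Autoantibodies and Karnofsky score are measured at only one of them.
- The targeted examination on Day 0 (6.3.6) does not list the Karnofsky score, so it does not fill that gap.

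**The case against.** Several stronger readings are tempting, and the documents do not support them.

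- **A reader might infer that no specimen exists near vaccination.** Plasma is stored on Day 0 (6.0 item 3m), and the table in 6.1 also marks pre-entry. What is missing is a scheduled test. A laboratory or analysis plan not shown here could assign the stored material to this purpose. The protocol does not do so, however. Appendix III describes one 2-mL citrate plasma aliquot, whereas 4.1.8 asks for a serum anti-ds-DNA result, so suitability is not shown. Testing stored plasma only after a positive Day 28 result would be selective.
- **A reader might infer that a positive Day 28 result cannot be linked to vaccination at all.** Subjects must be anti-ds-DNA negative at screening, so a later positive is a documented conversion since then. Its timing is uncertain, not unknowable. Nor would a Day 0 test prove cause in nine uncontrolled subjects.
- **A reader might argue that, because ANA up to 1:40 is allowed, a rise and not mere presence must be judged.** The endpoint concerns anti-DNA antibody, which must be negative at entry. The ANA allowance does not bear on it.
- **A reader might combine the longest interval with the entry breach.** If the 30-day heading governs, the gap is at most 58 days. The 118 to 120 days arise only where that heading is not enforced.

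It is also fair to say that three months is an outer limit, that a screening visit within 30 days satisfies every section, that the objective is one of monitoring, and that dose escalation (9.1.3) does not depend on it. These points limit the weight of the concern. They do not supply a near-entry test or remove the conflict between sections.

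**Conclusion.** The point holds in limited form. No autoantibody test is scheduled between screening and Day 28. The before-after interval for the anti-DNA endpoint can reach 118 to 120 days under the screening window alone, or 58 days under the 30-day limit, against 28 days with a Day 0 test. This weakens attribution of a conversion without removing it. The percentages of the interval that precede vaccination are shares of time, not risks. Any risk figure depends on an assumed background rate, as in the illustration.

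Separately, 4.1.8, 4.1.11 and 4.3.1 are inconsistent with the schedule in 6.0 and 6.1, because autoantibodies and Karnofsky score are not repeated at pre-entry. The Karnofsky mismatch concerns eligibility only and has no bearing on the antibody endpoint. The change is worth making because it is cheap and serves both the endpoint and compliance with the entry criteria.

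**What to change.** 1. Add a serum ANA and anti-ds-DNA test on Day 0, before vaccination, for every subject, and name it as the baseline for the anti-DNA endpoint. As an alternative, pre-specify paired testing of stored Day 0 and Day 28 plasma for all subjects, provided the assay is shown to be suitable for citrate plasma.
2. Reconcile 4.1.8, 4.1.11 and 4.3.1 with 6.0, 6.1 and 6.2.1. Either add autoantibodies and Karnofsky score to the pre-entry visit, or require these screening items within 30 days of entry and state that they are not re-checked at pre-entry.

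**Cost.** One added test occasion is 9 × 1 = 9 tests and two are 9 × 2 = 18, counting ANA and anti-ds-DNA together as one. Replacement subjects under 9.3 would add a few. Blood is already drawn at both visits, so the burden is a small laboratory cost, slightly more blood per draw and a protocol amendment.
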